### Theta burst stimulation protocol targeting antagonist and spastic muscles

The flexor carpi radialis (FCR) and extensor carpi radialis longus (ECRL) were selected as stimulation targets based on their established role as a primary agonist-antagonist pair responsible for the wrist flexion-extension imbalance in post-stroke upper limb spasticity. The central mechanistic hypothesis is that the spatial proximity of their cortical representations within the primary motor cortex enables the simultaneous modulation of this pair to preferentially target a shared cortical microcircuit, thereby regulating its excitatory-inhibitory balance to reset abnormal motor output (16).

All enrolled participants will receive iTBS, cTBS or sham stimulation before CPT session each weekday, Group 1: active iTBS to the antagonist plus sham cTBS to the spastic muscle. Group 2: sham iTBS to the antagonist plus active cTBS to the spastic muscle. Group 3: active iTBS to the antagonist plus active cTBS to the spastic muscle (Figure 2). The intervention will last for two consecutive weeks, with all procedures strictly adhering to the 2021 safety guidelines issued by the International Federation of Clinical Neurophysiology (17). Stimulation will be delivered with a MagTD transcranial magnetic stimulator (MagTD; Wuhan Yiruide Medical Device Technology Co., Ltd., Wuhan, China) and a figure-of-eight double coil (maximum field strength = 2 T, diameter = 9 cm). The coil center will be placed tangentially over the target muscle group, with the induced current directed downward. For the sham stimulations, we choose the Magstim's70 mm figure-of-eight double rapid2 air cooled coil (P/N 3910-00 S/NO 728) (18). The coils were identical in external appearance which ensured that the patients remained blind to the intervention (Figure 3).

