### Randomization and blinding

Randomization will be performed using a computer-generated random sequence by an independent statistician who is not involved in participant recruitment or outcome assessment.

Group allocation will be concealed in sequentially numbered, opaque, sealed envelopes, which will be opened by the intervention therapist immediately prior to the first treatment session. Both participants and outcome assessors will be blinded to group allocation. The intervention devices for active and sham stimulation will be identical in appearance and generate similar auditory and tactile sensations. For sham stimulation, the coil will be positioned at an angle that prevents effective peripheral stimulation while maintaining the same sound and vibration as active stimulation. Treating therapists delivering the stimulation will not be involved in outcome assessment or statistical analysis to maintain assessor blinding and minimize bias.

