**Figure 3 F3:**
[figure not shown]
Schematic of peripheral coil placement for the three trial arms. Group 1 **(top)**: Active iTBS over ECRL (antagonist) + sham cTBS over FCR (spastic muscle). Group 2 **(middle)**: Sham iTBS over ECRL + active cTBS over FCR. Group 3 **(bottom)**: Active iTBS over ECRL + active cTBS over FCR.

Peripheral stimulation intensity was individualized based on the peripheral motor threshold (PMT). For each participant, the coil was placed over the target muscle (FCR or ECRL) and the intensity was gradually increased from 20% of maximum stimulator output (MSO). The PMT was defined as the lowest intensity that consistently evoked a visible and palpable muscle twitch without causing pain or discomfort.

The final stimulation intensity was set at 110%−120% of the individual's PMT, corresponding to an average of 38.4% ± 9.2% MSO across all participants (range: 25%−52% MSO). This approach of titrating intensity relative to PMT is a established methodology in the field (11). The selected intensity range was designed to ensure adequate afferent input by consistently eliciting a robust M-wave, a key indicator of effective peripheral activation used in previous studies (19).

To ensure stimulation consistency across sessions, the evoked M-wave amplitude was recorded at the beginning and end of each treatment session using surface EMG (1,000 Hz sampling, 50–500 Hz bandpass filter). The target M-wave amplitude for effective stimulation was set between 5 and 10 mV, a range that indicates strong, suprathreshold activation of the peripheral nerve-muscle circuit, which is considered necessary for inducing plasticity. If the amplitude deviated by >20% from the baseline value, the stimulation intensity was recalibrated to maintain consistent peripheral activation. The overall safety of applying pTBS within these parameters in stroke survivors has been supported by systematic appraisal of the literature (20).

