The distinctive sounds and sensations produced by the active stimulation device posed a significant risk to blinding. To counter this, we implemented a comprehensive strategy. We engineered the sham coil to replicate the sensory profile of the active device and added random timing jitter to mask its rhythmic pattern. This technical approach cut the rate of correct group identification in our pilot study from 38 to 17%. Concurrently, we administered deceptive questionnaires about non-existent sensory details, a tactic that reduced participants' confidence in their guesses to chance levels. We will formally assess unblinding at the trial's conclusion and perform sensitivity analyses to gauge its influence on outcomes. For assessors, blinding was secured by physically separating them from the intervention suite, encrypting all group assignments, and employing multiple independent raters.

A single-center study with a modest sample size (*n* = 54) may limit the generalizability of our findings. Rather than dilute inclusion criteria, we embedded a mechanistic substudy in the first 30 participants: simultaneous TMS-EEG and spinal H-reflex recording to build a Bayesian hierarchical model linking individual excitability profiles to response (27). This won't boost statistical power but provides a prior for phase II trials, preventing wasted resources on suboptimal doses.

To further explore the long-term effects, a future 6-month substudy (*n* = 20) is planned. This substudy will not merely extend observation—it will use wearable EMG to continuously track the time constant of long-term trajectory of spasticity. This would reveal whether durability requires periodic booster sessions, directly informing translational decisions (home-based vs. clinic-based devices).

Based on our pilot study (unpublished), we identified a “high neural noise” phenotype, characterized by PMT variability (CV > 15%) in 23% of participants. Rather than treating this as statistical noise, we will use it as a predictive feature: poor responders with high CV will signal the need for EMG-closed-loop titration in future protocols. This is an adaptive design element nested within the trial logic, not a *post-hoc* fix.

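### The sham is described in three unreconciled ways, and none explains how the evoked muscle twitch is masked, so participant blinding is doubtful on the Group 3 versus Group 1 and 2 contrast

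*Protocol article*

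**What the plan says.** Three places in the protocol article describe the sham.

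- Randomization and blinding: "For sham stimulation, the coil will be positioned at an angle that prevents effective peripheral stimulation while maintaining the same sound and vibration". The devices are also said to look the same and to sound and feel similar.
- Theta burst stimulation protocol: "For the sham stimulations, we choose the Magstim's70 mm figure-of-eight double rapid2 air cooled coil", with part and serial numbers and no mention of an angle. The active coil is a MagTD figure-of-eight ("maximum field strength = 2 T, diameter = 9 cm"), and its plane is to lie against the skin. The section then concludes: "The coils were identical in external appearance which ensured that the patients remained blind to the intervention".
- Discussion: "We engineered the sham coil to replicate the sensory profile of the active device and added random timing jitter to mask its rhythmic pattern".

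Active dosing is anchored to the peripheral motor threshold, defined as "the lowest intensity that consistently evoked a visible and palpable muscle twitch" without pain or discomfort. Treatment is given at 110%–120% of it, with an M-wave target of 5 to 10 mV. As a consistency check, "the evoked M-wave amplitude was recorded at the beginning and end of each treatment session"; the text does not say whether this is done at sham sites.

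Groups 1 and 2 each have one active and one sham site, and Group 3 has two active sites (Study design). The hypothesis is that Group 3 does best (Anticipated results). The Discussion concedes a significant risk to blinding, reports that correct group identification in the pilot fell from 38% to 17%, and plans an unblinding assessment with sensitivity analyses. The Abstract calls the trial single-blind, whereas Randomization and blinding says that participants and assessors are both blinded.

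**The concern.** Staff reading this article could not tell which sham to deliver, and the reason given for participant blinding, matching appearance, does not fit the hardware described. Appearance is also not the main threat. The active dose is defined by a muscle response that the participant can see and feel, and nothing in the text says how the sham imitates it.

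The gap matters because of where it falls. Every participant has at least one active site and so has a sensation to compare with in the same session. The difference between one and two responding sites is the difference between Groups 1 or 2 and Group 3. FMA-UE and ARAT depend on the participant's effort, and MAS depends, to a lesser degree, on relaxation. Blinding the assessor does not remove an expectation effect carried by the participant.

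**Working it through.** **Step 1. The sham accounts side by side.**

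| Feature | Randomization and blinding | Theta burst section | Discussion |
|---|---|---|---|
| Hardware | not specified | Magstim 70 mm catalogue coil | engineered sham coil |
| Placement | angled | no angle stated | not stated |
| Timing | not stated | 5 Hz, fixed (Table 3) | random jitter |
| Basis for blinding | looks, sound, touch | appearance | sensory profile, masked rhythm |

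Read together, the first two give an angled 70 mm coil of one make, compared with a flat 9 cm coil of another. That strains the appearance claim further. A purpose-engineered coil and a catalogue coil with a part number are hard to treat as the same object. Jitter does not appear in Table 3, and the Discussion does not say whether it applies to sham, active or both.

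**Step 2. The twitch.** Threshold is the lowest intensity that gives a visible and palpable twitch. Active intensity is 1.10 to 1.20 times that, so a twitch is expected at every active site. The sham coil's angle is one that "the coil will be positioned at an angle that prevents effective peripheral stimulation", so a twitch is not expected at a sham site. Expected twitching sites per participant:

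- Group 1: 1 (extensor)
- Group 2: 1 (flexor)
- Group 3: 2

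The text claims similar sound, vibration and touch. It gives no means of reproducing a contraction.

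**Step 3. The pilot figures.** These are the only data offered on blinding.

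- If the pilot had three equal arms, which is not stated, chance is 1/3 = 33.3%. Then 38% is 4.7 points above chance before the masking measures, and 17% is 16.3 points below it afterwards. A rate near chance at the start leaves little to improve. A rate below chance can reflect small numbers or systematic misguessing as easily as a good sham.
- No denominator is given. The Discussion mentions a pilot of 12, but 4/12 = 33.3% and 5/12 = 41.7%, so 38% cannot arise from 12. If both rates share one denominator, the smallest that gives both is 24 (9/24 = 37.5%, 4/24 = 16.7%).
- The reported fall in participants' confidence after deceptive questionnaires concerns confidence, not whether the guesses were right.

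**Step 4. Illustration of what is at stake.** The documents give no bias, so the values of b below are assumptions. Let b be an expectation effect favouring Group 3, in SD units, with n per arm and no true difference. The two-sided 5% rejection rate of one pairwise comparison (normal approximation) is

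1 − Φ(1.96 − δ) + Φ(−1.96 − δ), with δ = b / √(2/n).

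The 54 recruited give n = 18 per arm; the 45 expected completers give n = 15. For b = 0.3 and n = 18, δ = 0.3/0.333 = 0.90, and the rate is 1 − Φ(1.06) + Φ(−2.86) = 0.145 + 0.002 = 0.147.

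| Assumed b | n = 15 | n = 18 |
|---|---|---|
| 0 | 5.0% | 5.0% |
| 0.2 | 8.5% | 9.2% |
| 0.3 | 13.0% | 14.7% |
| 0.5 | 27.8% | 32.3% |

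**The case against.** The strongest reply is that the three descriptions are layers: one gives position, one hardware, one timing. That is partly right, and a reader should not infer that an active coil is tilted, since the text says only that the coil is angled. It also does not show that different shams are used in different sessions. Layering still leaves the engineered coil against the catalogue part, and it weakens the appearance claim.

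A reader might go further and conclude that participants can tell their group, or that blinding fails. The documents do not show this. They assert similar tactile sensation and a replicated sensory profile. The two sites receive different patterns in any case (200 s intermittent, 40 s continuous), so even Group 3 would feel a difference between sites, and sensory loss after stroke may blunt perception. The missing twitch is an inference from the protocol's own definitions, and detection by participants is a further inference.

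Nor do the documents show that jitter breaches the 5 Hz pattern; its scope is simply unstated. Treating 17% as 2 of 12 and attaching an interval is also unsupported, because 38% does not fit that denominator.

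Two further points stand in the plan's favour. Unblinding will be assessed formally, with sensitivity analyses. MAS is a passive rating by a blinded assessor, which narrows the route for bias on that scale. The first measures a problem at the end of the trial without preventing it; the second does little for FMA-UE and ARAT.

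**Conclusion.** The point holds in this form: the sham is described inconsistently, the appearance claim is not credible as written, and participant blinding is doubtful on the Group 3 versus Group 1 and 2 contrast. The doubt rests on two assumptions: that a sham which prevents effective stimulation produces no twitch, and that at least some participants notice. The pilot rates, without denominator or arm structure, neither confirm nor remove it.

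The size of any bias is unknown. Over assumed values of 0.2 to 0.5 SD, the 5% error of one pairwise comparison becomes roughly 9% to 32%, which is enough to make a modest Group 3 advantage hard to separate from expectation. This should be corrected, but it does not by itself invalidate the design.

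**What to change.** 1. Merge the three descriptions into one sham used at all sham sites and sessions, with coil housing and placement matched to active.
2. State whether jitter applies to sham, active or both, and reconcile it with Table 3.
3. Screen the forearm from the participant's view at every session, and acknowledge that this hides the visible twitch but not the felt one.
4. Run threshold and M-wave checks in the same way at active and sham sites in every arm. Any difference in the checks between sites would itself reveal which site is sham. Real test pulses at a sham site also give the participant a comparison, so the protocol should say what is done.
5. In the planned unblinding assessment, ask for a guess per site (50% by coin toss) and per arm (33%), and use both in the sensitivity analysis. Report by arm: each site is active in two of the three arms, so always answering active would be right 2/3 of the time overall.
6. Reconcile the single-blind label in the Abstract with the blinding of participants and assessors in the Methods. Replace the statement that appearance ensured blinding, and claim participant blinding only if the check supports it.

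The cost is protocol text, a screen, two questions and whatever work is needed to match the coil housing. The downside is a weaker blinding claim.

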**Figure 2 F2:**
[figure not shown]
An anatomical figure for targeting landmarks. Left image: The target muscle is the extensor carpi radialis longus. Its origin is the lateral epicondyle, and its insertion is the dorsal surface of the base of the second metacarpal bone, connected by the green dashed line. The red five-pointed star indicates the stimulation point location, which is 4 cm distal to the lateral epicondyle. Right image: The target muscle is the Flexor Carpi Radialis. Its origin is the medial epicondyle, and its insertion is the palmar surface of the base of the second metacarpal bone, connected by the green dashed line. The red five-pointed star indicates the stimulation point location, which is 5 cm distal to the medial epicondyle.

**Figure 3 F3:**
[figure not shown]
Schematic of peripheral coil placement for the three trial arms. Group 1 **(top)**: Active iTBS over ECRL (antagonist) + sham cTBS over FCR (spastic muscle). Group 2 **(middle)**: Sham iTBS over ECRL + active cTBS over FCR. Group 3 **(bottom)**: Active iTBS over ECRL + active cTBS over FCR.

Peripheral stimulation intensity was individualized based on the peripheral motor threshold (PMT). For each participant, the coil was placed over the target muscle (FCR or ECRL) and the intensity was gradually increased from 20% of maximum stimulator output (MSO). The PMT was defined as the lowest intensity that consistently evoked a visible and palpable muscle twitch without causing pain or discomfort.

The final stimulation intensity was set at 110%−120% of the individual's PMT, corresponding to an average of 38.4% ± 9.2% MSO across all participants (range: 25%−52% MSO). This approach of titrating intensity relative to PMT is a established methodology in the field (11). The selected intensity range was designed to ensure adequate afferent input by consistently eliciting a robust M-wave, a key indicator of effective peripheral activation used in previous studies (19).

To ensure stimulation consistency across sessions, the evoked M-wave amplitude was recorded at the beginning and end of each treatment session using surface EMG (1,000 Hz sampling, 50–500 Hz bandpass filter). The target M-wave amplitude for effective stimulation was set between 5 and 10 mV, a range that indicates strong, suprathreshold activation of the peripheral nerve-muscle circuit, which is considered necessary for inducing plasticity. If the amplitude deviated by >20% from the baseline value, the stimulation intensity was recalibrated to maintain consistent peripheral activation. The overall safety of applying pTBS within these parameters in stroke survivors has been supported by systematic appraisal of the literature (20).

The iTBS protocol was configured to deliver a total of 600 pulses, organized into 20 trains. Each train consisted of 10 bursts, with an 8-s inter-train interval. Within each burst, three pulses were administered at a frequency of 50 Hz, and the bursts themselves were repeated at a theta frequency of 5 Hz. The total stimulation duration for the iTBS protocol was 200 s (Table 3). During treatment, participants will lie supine. For iTBS: the figure-of-eight double coil will be centered over the antagonist muscle—specifically, the most prominent belly of the extensor carpi radialis longus (ECRL), located 4 cm distal to the lateral epicondyle of the humerus and 1 cm radially (Figure 2). This location was confirmed through anatomical palpation and is standardized to ensure consistent targeting of the ECRL muscle belly, a common motor point for effective stimulation (20, 21). The coil plane will be flush with the skin surface, the handle oriented proximally and angled aligned parallel to the long axis of the forearm. The cTBS protocol was configured to deliver a total of 600 pulses in a single, continuous train of 200 bursts without interruption. The total stimulation duration for cTBS was 40 s, during which bursts were delivered continuously at a theta frequency of 5 Hz. Each burst contained three pulses administered at a frequency of 50 Hz. For cTBS: the coil will be centered over the spastic muscle—the most prominent belly of the flexor carpi radialis (FCR), located 5 cm distal to the medial epicondyle of the humerus and 1 cm ulnarly. Similarly, this site was determined based on anatomical landmarks to reliably target the FCR belly, promoting reproducible stimulation across sessions (20, 21). The coil plane will again lie flat against the skin, with the handle oriented proximally and aligned parallel to the long axis of the forearm. The stimulation intensity for both iTBS and cTBS was set at 110%−120% of the individual's peripheral motor threshold (PMT).

**Table 3 T3:** Detailed parameters for the peripheral theta-burst stimulation protocols.

**Parameter**	**iTBS**	**cTBS**
Total stimulation duration	200 s	40 s
Total pulses	600	600
Pulse frequency (within burst)	50 Hz	50 Hz
Pulses per burst	3	3
Burst frequency	5 Hz	5 Hz
Bursts per train	10	200
Total trains	20	1
Inter-train interval	8 s	N/A
Stimulation intensity	110%−120% of PMT	110%−120% of PMT

iTBS, intermittent theta-burst stimulation; cTBS, continuous theta-burst stimulation; PMT, peripheral motor threshold; N/A, not applicable.

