In recent years, our understanding of neuromodulatory mechanisms has continued to evolve. The “W-shaped” nonlinear model, originating from research on cognitive aging, posits that the relationship between cortical excitability and neural function is not linear (13). This model asserts that both excessively high and low states of cortical excitability are maladaptive, leading to impaired behavioral performance, while optimal cognitive function corresponds to an intermediate “optimal functional zone.” Although this model was developed in the cognitive domain, the core principle it reveals—the “excitability-function relationship” —likely represents a universal operating principle for neural networks. This is corroborated by the work of Buss et al., (14) which demonstrated that in cognitively healthy older adults, higher cognitive reserve is associated with lower motor cortex excitability. This suggests that a more optimized, moderate level of excitability forms the foundation for efficient neural processing. Critically, this principle provides a novel, integrative lens through which to understand post-stroke motor dysfunction. The classic post-stroke imbalance between hemispheres—characterized by hypoexcitability in the affected motor cortex and hyperexcitability in the unaffected hemisphere—precisely mirrors the two dysfunctional states at the extremes of the “W-shaped” model. Therefore, synergistically driving motor cortical excitability toward the central “optimal functional zone,” rather than merely applying unidirectional facilitation or inhibition, should constitute a more effective regulatory strategy. However, existing pTBS protocols have yet to leverage this theoretical framework. They typically lack a bidirectional design capable of simultaneously driving both hyper- and hypo-excitable neural circuits toward the “optimal functional zone” in an agonist-antagonist manner.

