Building on this framework, we designed an RCT to formally test these mechanisms and establish clinical feasibility. This protocol makes three contributions: (1) a standardized PMT titration method, (2) first RCT testing the W-shaped model through dual-site pTBS, and (3) a rigorous sham-controlled design. Primary objectives are to evaluate pTBS effects on spasticity/function, investigate neurophysiological mechanisms, and establish safety profiles. Secondary objectives include validating central-peripheral synergy, comparing single vs. dual-site stimulation, and generating effect sizes for future trials.

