## Discussion

The W-shaped excitability framework—where both hyper- and hypo-excitability impair function—doesn't map neatly onto post-stroke spasticity (28). Stroke does not produce a uniform excitability shift; it may create a spatially dissociated pathology characterized by spinal hyperexcitability in spastic flexors and, as suggested by our pilot data and others, cortical hypo-excitability in their antagonists; accordingly, this “split-modulation” approach emerged from pilot data (*n* = 12) where cTBS alone reduced MAS scores without improving ARAT, and iTBS alone did the opposite—suggesting that resetting the network requires both levers (28).

Parameter selection bypassed convention in favor of peripheral nerve physiology. The 110%−120% PMT intensity—averaging 38.4% MSO in our pilot—produced a 15%−20% increase in M-wave amplitude, the narrow band where Ia fibers activate without recruiting nociceptive afferents (20). Below this threshold, spinal plasticity markers (H-reflex suppression) vanished on TMS-EEG (27); above it, tolerance dropped below 70% within 15 min. The 600-pulse dose was selected based on a balance between efficacy and safety. The IFCN guidelines recommend a maximum of 800 pulses per session for peripheral TBS protocols to ensure safety (17). Furthermore, doses of 400–800 pulses have been commonly employed in prior rPMS studies and are considered necessary to induce consistent neurophysiological changes at the spinal level, such as H-reflex suppression (11, 21). Thus, our 600-pulse protocol operates within established safety boundaries while aligning with doses used in effective rPMS studies.

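### The arm contrasts cannot separate opposite polarity from muscle, number of active sites or pulse count, so a Group 3 advantage alone is not evidence for the bidirectional (W-shaped) mechanism

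*Protocol article*

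**What the plan says.** The Methods section on the theta burst protocol defines the combined arm as "Group 3: active iTBS to the antagonist plus active cTBS to the spastic muscle". Groups 1 and 2 keep the same placement of pattern on muscle; in Group 1 the cTBS is the sham component, and in Group 2 the iTBS is. The coil-placement text ties each pattern to one muscle: "For iTBS: the figure-of-eight double coil will be centered over the antagonist muscle" (ECRL) and "For cTBS: the coil will be centered over the spastic muscle" (FCR). The Abstract, the study design section and the Figure 3 legend agree. Table 3 gives 600 pulses for each pattern.

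The Introduction describes iTBS as facilitating and cTBS as inhibiting. It says of earlier peripheral protocols: "They typically lack a bidirectional design capable of simultaneously driving both hyper- and hypo-excitable neural circuits". Its last paragraph then says the trial was designed to put these mechanisms to a formal test, and counts among its contributions that it is the "first RCT testing the W-shaped model through dual-site pTBS". The same paragraph lists a comparison of single-site with dual-site stimulation as a secondary objective. The Abstract's anticipated results expect Group 3 to do best, and expect its gains, through their correlation with neurophysiological change, to support the central-peripheral synergy model. The limitations in the Discussion do not mention that pattern and muscle always go together.

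**The concern.** The theory is about direction: raise excitability on one side of the muscle pair and lower it on the other. To attribute a result to direction, some participants would have to receive two active sites without opposite patterns, or a pattern on the other muscle. None of the 54 do. A Group 3 advantage could come from opposite polarity, from treating a second muscle, or from delivering more pulses.

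What is at stake is the conclusion. A positive result could be reported as support for bidirectional modulation and carried into the larger trials that the Abstract anticipates, although the arm contrasts had not isolated that mechanism. The estimates themselves and the error rates are not affected.

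**Working it through.** The plan gives no figure to reproduce on this point. The check is whether the effects can be identified from the three arms.

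**Inputs.** Arm definitions and coil sites come from the theta burst section. Pulse counts come from the same section and Table 3:
- iTBS: 20 trains × 10 bursts × 3 pulses = 600.
- cTBS: 200 bursts × 3 pulses = 600.

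Both reproduce the stated totals.

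**Step 1: arm-level indicators (Groups 1, 2, 3).**

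| Quantity | G1 | G2 | G3 |
|---|---|---|---|
| Active iTBS | 1 | 0 | 1 |
| Active stimulation of ECRL | 1 | 0 | 1 |
| Active cTBS | 0 | 1 | 1 |
| Active stimulation of FCR | 0 | 1 | 1 |
| Opposite polarities together | 0 | 0 | 1 |
| Two active sites | 0 | 0 | 1 |
| Active pulses per session | 600 | 600 | 1200 |
| Active pulses/600 − 1 | 0 | 0 | 1 |

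Rows 1 and 2 are identical, and so are rows 3 and 4. Opposite polarity, two active sites and pulses/600 − 1 are also identical.

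**Step 2: rank.** A model with intercept, two active sites and opposite polarity has three columns but rank 2. At site level there are six arm-by-site cells, with columns for intercept, active, site and pattern. The rank is 3 of 4, and the correlation of site with pattern is 1.00.

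**Step 3: what the contrasts contain.** Write a for the effect of a second active site with its pulses, whatever the pattern, and p for the extra effect of the patterns being opposite. Then Group 3 − Group 1 = a + p, with a and p referring to adding FCR. Group 3 − Group 2 has the same form for adding ECRL. Each contrast is one equation in two unknowns, so the data fix the sum and not the split. More participants do not change this.

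**Step 4: what would break the alias.** If dual-active arms with one pattern on both muscles are added to the matrix, intercept, two sites and opposite polarity have rank 3 of 3. At 18 per arm, four arms would be 72 participants and five would be 90. This is arithmetic to show the cause, not a proposal. A double-sham arm would not help here, because pattern and muscle would still be identical columns.

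**Step 5: the other mechanistic data.** MEPs are taken from a thumb muscle (APB) of the paretic limb, with stimulation of the affected hemisphere only, as a general index of corticospinal excitability. They cannot show opposite shifts in the FCR and ECRL circuits. The planned Spearman correlation relates change in MEP amplitude (or cortical silent period) to change in FMA-UE. The Discussion's substudy (TMS-EEG and H-reflex in the first 30 participants) may show the direction of change after a given muscle-pattern pair. It draws on the same three arms, so it has no swapped or same-pattern cell to show that the pattern was responsible.

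**The case against.** The strongest reply is that the pairing is the intervention. The hypothesis is that Group 3 beats Groups 1 and 2, and one objective is single against dual site. The arms answer both. Crossed cells would, on the article's own rationale, facilitate the spastic muscle or inhibit its antagonist, so leaving them out is an ordinary choice in a trial of components against their combination. All of this stands, and no new arm is asked for. It does not cover the further claim in the Introduction that the trial formally tests the mechanism.

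The second reply is that the closing paragraph of the Discussion rests the model on single-subject excitability shifts and calls group means secondary. That also stands in part: the article does not rest the W-shaped model on arm means alone. But for the reasons in the working, those measures can support the model only in an exploratory way.

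Four stronger readings are tempting and are not supported:
- *The randomised comparison is invalid.* It is not. Superiority over both arms would show that each component adds something to the other.
- *One pattern on both muscles would give the same result.* The documents do not show this and describe the patterns as polarity-specific. The arms only fail to exclude it.
- *Stimulation time (200 s against 40 s) is a further confounder.* The 200 s include the pauses that define iTBS. Pulse delivery is 10/5 = 2 s per train × 20 = 40 s for iTBS and 200/5 = 40 s for cTBS, hence about 40, 40 and 80 s in Groups 1 to 3.
- *The Discussion already concludes that polarity matters.* Its phrase "suggesting that resetting the network requires both levers" is a hedged reading of pilot data, not a conclusion from these arms.

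**Conclusion.** The point holds, limited to mechanistic attribution. The aliasing of pattern with muscle, and of opposite polarity with two active sites, is complete and does not depend on sample size. There is no numerical bias to report: the share of a Group 3 benefit due to polarity is not identifiable from the arm contrasts. An unseen full protocol or analysis plan could not change this for these arms, because no analysis separates identical columns.

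Two assumptions apply. Sham is taken to deliver no effective peripheral stimulation, as the blinding section intends. The 1200 pulses in Group 3 take the Methods and Table 3 at their word that each pattern delivers 600; the Abstract's 600 per session could be read as a total. On that reading pulse count might drop out of the list, but muscle and number of active sites would stay aliased with polarity.

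The change should be made because the mechanistic claim is printed in the Introduction and is cheap to correct.

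**What to change.** 1. In the last paragraph of the Introduction, replace the claim that the trial formally tests the bidirectional or W-shaped mechanism. State that the arm comparisons estimate the benefit of adding the second muscle-pattern pair: active cTBS over FCR on top of active iTBS over ECRL, and the reverse. Add that a Group 3 advantage alone is not evidence for polarity-specific modulation.
2. Word the Abstract's anticipated results to match.
3. In the Discussion, list as a limitation that the arms do not separate polarity from muscle, number of active sites or pulse count. Describe the MEP, H-reflex and TMS-EEG analyses, including the single-subject test of the model in the closing paragraph, as exploratory support.

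The pilot wording in the Discussion need not change. The cost is a weaker mechanistic claim. Arms, sample size and regimen stay as they are, and the question of polarity is left to a later design that does not tie pattern to muscle.
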